## 2.2 Study Design

This is a phase I randomized, blinded, placebo-controlled study of the safety and acceptability of the vaginal formulation of UC-781 gel, when administered rectally, to be conducted in 36 adults (12 per group) residing in the Los Angeles, CA area. All of the participants will be HIV negative. The study design is summarized in the Schema above and the Schedule of Events in Appendix I.

This study will involve 2 stages of treatment. Each treatment stage is independent of the other. **This study aims to examine the effects of 2 different dosing regimens, NOT cumulative toxicity over both stages.** Participants will undergo extensive evaluation during 5 study visits over an approximately 7-14 week period. In addition, acceptability assessments will be completed at baseline and Visit 5.

Interested participants will enter a screening period, which includes (Visit 1) and if necessary a medication washout period. Subjects, who are deemed eligible after this screening period, will return for a baseline evaluation (Visit 2), including clinical evaluation and mucosal specimen collection, as well as a baseline behavioral assessment (BBQ). The BBQ questionnaire will be administered by CASI. Subjects may complete the web-based CASI in the privacy of their own home. If a subject does not have access to the internet, prefers to complete the BBQ at the study site, or requires assistance in using the CASI, they will be accommodated at the study site.

After completing Visits 1 and 2, eligible subjects will be randomized to one of three groups: 0.1% UC-781 gel, 0.25% UC-781 gel, or a placebo gel (12 per group). A subset of 9 subjects (3 from each group) will also participate in a pK sub-study, which will include 6 timepoints (Visit 3- pre, 0.25 hr, 2 hr, 4 hr, Visit 3A- 24 hr, and Visit 5- 1 day post-QD dose draw). During randomization, study staff will be notified if the participant is randomized to the pK sub-study. Subjects will be randomized in blocks of 3, one per group to minimize imbalance in treatment assignments. The first three subjects enrolled in each of three treatment groups will be selected for the pK sub-study. It is possible that participants may refuse to participate in the sub-study, and spots will continue to be offered as needed.

Once randomized, subjects will return to the clinic (Visit 3), where a single dose of the study gel (Treatment Stage 1) will be administered after a preparatory Normosol-R pH7.4 enema. Within approximately 30 minutes, mucosal specimens will be obtained, including post-dose lavage, sponge specimens and colorectal biopsies. Subjects will receive a safety follow-up phone call.

Subjects will return to the clinic for Treatment Stage 2 Clearance (Visit 4), in the week prior to beginning Treatment Stage 2. If given clearance, the subject may begin Treatment Stage 2.

In Treatment Stage 2, subjects will begin to self-administer once daily outpatient doses of the study gel for 7 days. Subjects will receive a follow-up safety phone call mid-way through

Stage 2. After completion of Stage 2 the subject will complete a Product Acceptability Questionnaire (PAQ) by CASI and return to clinic for evaluation and specimen collection (Visit 5). Subjects will receive a safety follow-up phone call.

After completion of Visit 5, subjects will be contacted by an interviewer to complete an in-depth phone interview regarding product acceptability. [The complete results of these interviews will not be shared with the rest of the research staff until the blind has been broken, as subjects may unwittingly reveal information that would break the blind. Only preliminary data that does not compromise the blind may be shared prior to data lockdown and unblinding.]

#### PRN visits

- Any complications that arise may require further clinical evaluation.

### **3.0 STUDY POPULATION**

Thirty-six HIV negative adults will be selected for the study according to the criteria in Sections 3.1 and 3.2. Participants will be recruited, screened, and enrolled concurrently as described in Section 3.3, 5.1, and 5.2.

Issues related to participant retention and withdrawal from the study are described in Sections 3.4 and 3.5, respectively.

#### **3.1 Inclusion Criteria**

Men who meet the following 10 criteria and women who meet the following 12 criteria are eligible for inclusion in the study:

1.  $\geq$  Age of 18
2. HIV-1 status antibody negative as documented at screening
3. Understands and agrees to local STI reporting requirements
4. Able and willing to communicate in English
5. Able and willing to provide written informed consent to take part in the study
6. Able and willing to provide adequate information for locator purposes
7. Availability to return for all study visits, barring unforeseen circumstances
8. A history of consensual RAI at least once in lifetime\*

*\*Required to assure that subjects have a context for the acceptability assessments.*

9. Willing to abstain from insertion of anything per rectum other than the study gel for the 1 week prior to treatment, 1 week prior each flexible sigmoidoscopy (i.e. during week of study gel use), and 1 week after each flexible sigmoidoscopy.
10. Must agree to use condoms for the duration of the study

**In addition to the criteria listed above, female participants must meet the following criteria:**

11. Negative pregnancy test
12. Post-menopausal or using an acceptable form of contraception (e.g. barrier method, IUD, hormonal contraception, surgical sterilization, or vasectomization of male partner). If the female subject has female partners only, the method of contraception will be noted as a barrier method in the study documentation.

### **3.2 Exclusion Criteria**

Individuals who meet any of the following criteria at screening will be excluded from the study:

1. HIV positive at baseline
2. History of inflammatory bowel disease
3. Active inflammatory condition of the GI tract at baseline
4. Active rectal infection at baseline
5.  $\geq$  Grade 2 laboratory abnormality at baseline
6. History of an underlying cardiac arrhythmia or renal disease that may be exacerbated by electrolyte abnormalities.
7. History of severe or recent cardiac or pulmonary event
8. History of a large aortic aneurysm
9. History of significant gastrointestinal bleeding
10. Allergy to methylparaben, propylparaben, sorbic acid
11. History of alcoholism or IV drug abuse
12. Unwillingness to refrain from chronic use of aspirin and NSAIDs.
13. Use of warfarin or heparin
14. Use of systemic immunomodulatory medications within 4 weeks of Visit 2
15. Use of rectally administered medications, with the exception of over-the-counter enemas, within 4 weeks of Visit 2
16. Use of product containing nonoxyl-9 rectally within 4 weeks of Visit 2

17. Use of any investigational products within 4 weeks of Visit 2
18. Any other clinical condition or prior therapy that, in the opinion of the investigator, would make the patient unsuitable for the study or unable to comply with the study requirements. Such conditions may include, but are not limited to, current or recent history of severe, progressive, or uncontrolled renal, hepatic, hematological, gastrointestinal, endocrine, pulmonary, neurological, or cerebral disease.

**In addition to the criteria listed above, female participants will be excluded if they meet any of the following criteria:**

19. Pregnancy
20. Breastfeeding
21. Female of child-bearing potential unwilling to use acceptable form of contraception

### **3.3 Recruitment Process**

Recruitment will occur using four main strategies:

- i. Clinician-patient referrals;
- ii. Use of existing “study registries” that contain the names and phone numbers of individuals who have given informed consent to be reached for future studies for which they may be eligible.
- iii. Participant referrals (participants refer their friends or partners who may meet eligibility criteria); and
- iv. Passive self-referral: interested individuals see a study poster or brochure advertising the study and call the study site directly.

Study staff will meet as needed to discuss current recruitment status, targets, and strategies. Staff also will follow-up with all persons who express an interest in the study to ensure that screening appointments are scheduled and carried out in a timely manner.

### **3.4 Participant Retention**

Once a participant enrolls in this study, the study site will make every effort to retain him/her for the duration of follow-up in order to minimize possible bias associated with loss-to-follow-up. The study staff is responsible for developing and implementing local standard operating procedures to target this goal. Components of such procedures include:

- ⊙ Thorough explanation of the study visit schedule and procedural requirements during the informed consent process, and re-emphasis at each study visit;
- ⊙ Thorough explanation of the importance of all three treatment phases to the overall success of the study;
- ⊙ Use of appropriate and timely visit reminder mechanisms (via email and/or telephone); and
- ⊙ Immediate and multifaceted follow-up on missed visits.

### 3.5 Participant Withdrawal

Regardless of the participant retention methods just described, participants may voluntarily withdraw from the study for any reason at any time. The Investigator also may withdraw participants from the study in order to protect their safety (e.g. pregnancy, diagnosis of colon cancer, ulcerative colitis) and/or if they are unwilling or unable to comply with required study procedures.

Participants also may be withdrawn if the IRB, study sponsor, government or regulatory authorities terminate the study prior to its planned end date.

Every reasonable effort will be made to complete a final evaluation (as described in Section 5) of participants who terminate from the study prior to the final visit, and study staff will record the reason(s) for all withdrawals from the study in participants' study records. Participants who withdraw or are withdrawn prior to receiving study product will be replaced. Participants who withdraw or are withdrawn after receiving study product will not be replaced.

## 4.0 STUDY PRODUCT CONSIDERATIONS

### 4.1 Drug Characteristics

UC-781 is the code name for N-[4-chloro-3-(3-methyl-2-butenyloxy)phenyl]-2-methyl-3-furancarbothioamide. UC-781 is a thiocarboxanilide pentenyloxy ether derivative of the carboxanilide class of compounds. It is a pale yellow powder with a molecular weight of 335.84 AMU and has low miscibility in water.

### 4.2 Study Product

UC-781 Gel 0.1% is an off-white to light yellow aqueous gel formulation containing 0.1% (w/w) UC-781, Carbomer 974P, methylcellulose, glycerin, purified water and common preservatives (methylparaben and propylparaben). It is adjusted to pH 5.2. The human dose is 3.5 g (approximately 3.5 ml). UC-781 Gel 0.1% is packaged in an overwrapped, single dose, prefilled applicator.

UC-781 Gel 0.25% is a light yellow aqueous gel formulation containing 0.25% (w/w) UC-781, Carbomer 974P, methylcellulose, glycerin, purified water and common preservatives (methylparaben and propylparaben). It is adjusted to pH 5.2. The human dose is 3.5 g (approximately 3.5 ml). UC-781Gel 0.25% is packaged in an overwrapped, single dose, prefilled applicator.

Control Gel is a clear aqueous gel formulation containing non-active substances: sodium chloride, hydroxyethyl cellulose, sorbic acid, sodium hydroxide and purified water. It is adjusted to pH 4.4. The human dose is 3.5 g (approximately 3.5 ml). Control Gel is packaged in an overwrapped, single dose, prefilled applicator.

This control gel has been used in the vaginal UC-781 trials and animal studies. Although the pH of the control gel is not the same as the UC-781 gel, it has been selected for consistency. The normal pH of the rectum is ranges between 6.1-7.5. However, as a natural protection from secreted bile acids, the rectum secretes bicarbonates contributing to a significant buffering capacity. This buffering capacity should be able to equilibrate small differences in pH between the study products.

### 4.3 Product Supply and Distribution

Supplies of gel will be shipped to the investigational pharmacy in boxes each containing 8 single-use vaginal applicators. These materials will be prepared under Good Manufacturing Practice (GMP) conditions by Dow Pharmaceutical Sciences, Inc, Petaluma, CA for CONRAD. Product will be shipped to the site under IATA and OSHA standards.

The overwrap for each applicator will be labeled with "Caution: New Drug – Limited by Federal (United States) law to investigational use." A single, blinded label will be affixed to each box. The kit will have an outside two-part, tear-off label. Labels will include the following additional information: randomization number, protocol number, storage conditions and dosing instructions. Only the investigational pharmacy will unblind to group throughout the study.

Supplies of UC-781 0.1% gel, UC-781 0.25% gel and Control gel are to be stored between 15 - 30°C in a secure area. Subjects will be instructed to store the gel at room temperature and away from direct light. The product has been shown to be stable for 6 months at room temperature, and 6 months at up to 40°C.

### 4.4 Dose Regimen

Each treatment stage is independent of the other.

Treatment Stage 1- After a preparatory Normosol-R pH7.4 enema, subjects will receive one rectally-administered dose of the study gel approximately 30 minutes prior to flexible sigmoidoscopy. The dose will be delivered via the provided applicator.

Full 7-day recovery period

#### Up to 3 weeks later:

Treatment Stage 2- Subjects will self-administer one dose of the study gel per rectum QD, preferably at the same time of day, for 7 days.

Study staff will review instructions for dispensing, administering, and storing investigational products with each participant prior to discharge from Visit 4.

### 4.5 Product Accountability

The investigational pharmacy at the site is required to maintain a complete record of all study products received from the manufacturer and subsequently dispensed and to monitor product expiration dates. All unused study products are to be returned to the study site. At the end of the study, specific instructions will be provided for the return or destruction of the study products by the study site. All drug returned and destroyed will also be recorded on the site accountability logs.

### 4.6 Adherence Assessment

Participants will be given a Product Use Log at the time product is dispensed. A member of the study staff will complete the header information, which will include the protocol

number and PID copied from the product label. After confirming that the header information is correct and the name on the pharmacy label is the participant's name, the staff member dispensing the study product will sign the log.. The subject will then be asked to complete the log indicating each dose used, the date and any additional comments regarding missed or lost doses. The Product Use Log will be collected at Visit 5 and reviewed by study staff. In addition, on approximately Day 4 of Treatment Stage 2, subjects will receive an interim follow-up call during which adherence will be assessed.

#### **4.6.1 Definition and Management of Non-Adherence**

Non-adherence is defined as missing a product dose. Missed doses will not be replaced. Non-adherent participants will be asked their reasons for non-adherence and this information will be recorded on source documents. If the subject discontinues the investigational product due to an AE, the subject will not be considered non-adherent. See Section 6.0 for Safety Monitoring.

#### **4.7 Concomitant Medications**

Concomitant medications are defined as medications taken within 4 weeks prior to enrollment (Visit 2) and throughout the study. Concomitant medications will be permitted with the exception of those prohibited under the inclusion/exclusion criteria. All concomitant medications, including dose changes, will be reported in the source documents and case report forms.

### **5.0 STUDY PROCEDURES**

An overview of the study visits and procedures schedule is presented in Appendix I. Participant accrual will take approximately 9-12 months and each participant will be on study for approximately 7-14 weeks. The total duration of the study will be approximately 18 months. Presented below is additional information on visit-specific study procedures. Detailed instructions to guide and standardize all study procedures will be provided in the study-specific procedures manual. All routine laboratory tests (HIV-1 antibody test, syphilis test, assays for rectal HSV, Chlamydia, and gonorrhea) will be conducted by the CLIA certified UCLA Medical Center Clinical Laboratory or a referral laboratory contracted through the UCLA Medical Center. All laboratory results will be reported to the trial participants once the results are available. Participants who receive unexpected results such as HIV seropositivity and/or rectal infection will be referred to available sources of medical and psychosocial care for appropriate support, counseling, clinical assessment, and treatment.

#### **5.1 Visit 1- Screening Visit (up to 1 month prior to Enrollment Visit)**

Written informed consent will be obtained before any screening procedures are initiated. For potential participants who do not meet the study eligibility criteria (e.g. the subject tests positive for HIV), the screening process will be discontinued when ineligibility is determined. Subjects not meeting the eligibility may be re-screened at a later date, if appropriate, as in the case of a required medication washout period. If a participant is not enrolled within 1 month of signing the informed consent form, the screening process must be repeated.

### 5.1.1 Non-clinical Procedures

- ⊗ Obtain informed consent
- ⊗ Assign screen ID number
- ⊗ Assess eligibility for study based on inclusion/exclusion criteria
- ⊗ Collect locator and demographic information
- ⊗ Provide HIV pre-test counseling
- ⊗ Give subject copies of all consent forms with investigators' contact information
- ⊗ Give concomitant medication logs with thorough explanation for use.
- ⊗ Review precautions:

-All participants should refrain from taking medications that may prolong bleeding, such as aspirin-containing products and/or NSAIDS for the 72 hours prior to and following flexible sigmoidoscopy and biopsy. Acetaminophen is permitted.

-All participants should abstain from insertion of anything per rectum other than the study gel for the 1 week prior to treatment, 1 week prior to each flexible sigmoidoscopy (i.e. during week of study gel use), and 1 week after each flexible sigmoidoscopy.

-Explain to participant that if in the course of the endoscopy the gastroenterologist sees signs of pathology, such as a polyp, the subject will be given the recommendation to follow-up with their primary care provider for evaluation; i.e. neither polyps nor any other pathology will be removed/treated by the research staff as part of the clinical trial. If the participant does not have a primary care provider, the study staff will provide them with a referral, but the study will not assume the cost of evaluation or treatment. It is recommended that all participants establish a relationship with a primary care provider prior to participation in this study. Participants will be withdrawn from the study pending further evaluation, but may be re-screened after evaluation as appropriate.

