#### ● Histopathology

Rationale: Endoscopy will be performed for the sole purpose of obtaining biopsy specimens at baseline, following single exposure, and following one week of QD exposure. Samples will be obtained at each flexible sigmoidoscopy and set aside for batch sectioning and H&E staining. Slides will be reviewed and scored by a qualified pathologist using the qualitative scoring system (see Appendix III) developed for the HPTN 056 study and adapted from validated scoring systems used in inflammatory bowel disease (IBD).

This scoring system is intended to improve upon the coarse scoring system used in past studies. Prior to the HPTN 056 study, one rectal microbicide study using histological data, employed a simple scoring system of normal, slightly abnormal, or abnormal. Using this histological system 69% of the placebo recipients and 89% of the N-9 recipients had slightly abnormal or abnormal rectal biopsies. The scoring system developed for the HPTN 056 study might provide better discrimination between abnormal and normal histology.

These indices are research measures only and will not be available or used in real-time to make clinical decisions, but will be analyzed as a secondary endpoint. In the immunologically responsive rectum, histologic assessment alone may be inadequate to evaluate subclinical cellular alterations in mucosal integrity. However, histology will inform in part the safety profile of the study products.

Histology is preferable to visual inspection which is a coarse measurement of mucosal health for several reasons 1) the wide spectrum of normal mucosal appearance, 2) inter-observer variability, 3) intra-observer variability. The single-cell rectal lining is easily damaged and quickly repairs. Presence of epithelial cells in effluent is normal; mucosal redness, flushing, loss of vascular pattern and even small erosions may all be normal variants and/or a result of colonic preparations. Should any significant abnormalities be noted during the exam, they will be recorded as adverse experiences (see Appendix IV and V Toxicity Tables), but endoscopic appearance will not be a study endpoint.

- Microflora

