### 6.3 Adverse Experience Reporting Requirements

Study participants will be provided with a list of danger signs and a 24-hour telephone number. Participants will be instructed to contact the study clinician to report not only danger signs, but also any events they may experience, except for life-threatening events, for which they will be instructed to seek immediate emergency care. Depending on the severity of the event, the clinician will instruct the participant to present to the study site (for more mild events) or to an emergency room (for more serious events) for immediate evaluation. Where feasible and medically appropriate, participants will be encouraged to seek medical care where the study clinician is based, and to request that the clinician be paged or otherwise contacted upon their arrival. With appropriate permission of the participant, records from all non-study medical providers related to such events will be obtained and required data elements will be filed with the source documentation. All participants reporting an AE will be followed clinically, until the AE resolves (returns to baseline), stabilizes or their last study visit. Subjects may be followed for longer periods of time per the discretion of the investigator, DAIDS, and the sponsor.

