### EAE Reporting Period

AEs must be reported on an expedited basis at the Standard Level during the Protocol-defined EAE Reporting Period, which is:

- The entire study duration for an individual subject (from enrollment until study completion or discontinuation of the subject from study participation for any reason).

After the end of the Protocol-defined EAE Reporting Period stated above, sites must report serious, unexpected, clinical suspected adverse drug reactions if the study site staff becomes aware of the event on a passive basis, i.e., from publicly available information.

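### The Section 5.1.1 rule withdrawing participants with pathology seen at endoscopy is not limited to pre-dose findings; applied at Visit 3 it would merge stopping gel with leaving the study

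*Protocol*

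**What the plan says.** The rule is in Protocol Section 5.1.1, in a list of precautions to go over with the participant at screening. It covers signs of pathology seen during endoscopy, gives a polyp as the example, refers the person to primary care, and ends: "Participants will be withdrawn from the study pending further evaluation, but may be re-screened after evaluation as appropriate". No visit, cause or severity is named. The Section 5.1.1 precautions are gone over again at Visits 2, 3, 4 and 5 (Sections 5.2.1, 5.3.1, 5.5.1 and 5.7.1).

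Other sections bear on the same participant:

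- Section 2.1.2, Histopathology: "Should any significant abnormalities be noted during the exam, they will be recorded as adverse experiences".
- Section 3.5: "The Investigator also may withdraw participants from the study in order to protect their safety". It also says "Participants who withdraw or are withdrawn after receiving study product will not be replaced", and promises reasonable effort at a final evaluation.
- Section 6.3: "All participants reporting an AE will be followed clinically, until the AE resolves (returns to baseline), stabilizes or their last study visit". Beyond that, "Subjects may be followed for longer periods of time per the discretion of the investigator, DAIDS, and the sponsor".
- Section 6.4.1: the expedited adverse event (EAE) reporting period runs "from enrollment until study completion or discontinuation of the subject from study participation for any reason". After it, serious, unexpected suspected reactions must be reported "if the study site staff becomes aware of the event on a passive basis".
- Section 6.4.2: serious events possibly associated with the drug, expected or not, are reported immediately, and serious events are followed. No cut-off by participation is stated.

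**The concern.** Stopping product and leaving the study are different decisions. A participant with a visible rectal lesion may well need to stop gel and be spared further biopsies. That is no reason to end safety observation, and after a first dose it is a reason to continue it. Section 8.3 says this formulation has not been tested rectally in humans before, and safety is a primary objective. If the gel did injure the mucosa, the Visit 3 sigmoidoscopy is the first place it could be seen, and the later course of that lesion would be some of the most useful safety information in the trial. A mandatory withdrawal rule without a pre-dose limit would take that participant out of scheduled observation just then.

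**Working it through.** **The plan's only sample-size figures.** Section 7.4 gives the chance of at least one event in 12 subjects. With 1 − (1 − p)^12, p = 0.20 gives 1 − 0.80^12 = 0.931 (stated as more than 90%), and p = 0.01 gives 1 − 0.99^12 = 0.114 (stated as 11%). Both reproduce. The point does not rest on them, so the rest of the check is a reading of the text.

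**Which endoscopies the rule can reach.** Visit 1 has anoscopy only (Section 5.1.2). Flexible sigmoidoscopy is done at Visits 2, 3 and 5 (Sections 5.2.2, 5.3.2 and 5.7.2). Two of these three follow dosing.

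**The order at Visit 3.** Gel is given at T = 0 and sigmoidoscopy follows at about 30 minutes (Section 5.3.2). Any lesion seen is therefore a post-dose observation, whatever its cause.

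**Two instructions for one lesion.** Section 2.1.2 makes a significant abnormality an adverse experience, which Section 6.3 then follows. Section 5.1.1 takes the participant off study. If the withdrawal is meant as a temporary hold, the only stated way back is re-screening. Section 5.1 uses that term for people who did not meet eligibility, and exclusion 17 bars investigational product within 4 weeks of Visit 2. Neither fits someone already randomised and dosed.

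**What ends and what stays for that participant.**

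| Lost if the rule is applied | Still in place |
|---|---|
| Visit 4, with AE assessment and examination including anoscopy, and other scheduled follow-up | The lesion, recorded and graded as an AE, and the Visit 3 samples |
| Assured follow-up of non-serious AEs beyond a best-effort final evaluation (3.5, 6.3) | Attempted call about one day after Visit 3, with further evaluation of any AE (5.4); PRN visits (2.2); discretionary longer follow-up (6.3) |
| The active EAE reporting period (6.4.1) | Immediate reporting and follow-up of serious events (6.4.2) |

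**How the Protocol treats comparable findings.**

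- A laboratory abnormality of Grade 2 or higher at Visit 3 bars Stage 2, with possible repeat testing, but does not itself require withdrawal from the study (Section 5.6).
- Stopping product for an AE is recognised as an event of its own (Section 4.6.1).
- A positive STI result or HSV lesions at Visit 5 do not cancel the visit, which goes ahead for safety (Section 5.7.2).

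The endoscopy sentence does not make the separation that these three make.

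**The window affected.** The earliest Stage 2 start is after the 7-day recovery, so Day 8 falls 7 + 7 = 14 days after Visit 3. The latest start is 3 weeks after Visit 3, so Day 8 falls 21 + 7 = 28 days after it. Each is ± 1 day. Nominal check: Week 6 − Week 2 = 4 weeks = 28 days.

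**What not to count.** Stage 2 exposure, the post-Stage 2 endpoints and most acceptability data would be lost anyway if gel were rightly held. At Visit 5 dosing is complete, so the effect there is minimal.

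**The case against.** The strongest reply is that the sentence was never meant for post-dose lesions. It is screening counselling about incidental disease and referral. It speaks of a single endoscopy, while the neighbouring precaution refers to each sigmoidoscopy, and re-screening makes sense only before dosing. Repeating the precautions at later visits is a generic cross-reference; it appears even at Visit 4, which has no sigmoidoscopy. Most of this stands: Visit 2 is probably what was intended. But the rule is mandatory and the limit is not written, so the remedy is to write it.

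The contrast with the discretionary wording in Section 3.5 is weak evidence. Section 3.5 lists pregnancy among its discretionary examples, while Section 6.3 makes withdrawal for pregnancy compulsory. Section 6.3 also follows a withdrawn pregnant participant to outcome, so withdrawal need not end follow-up. There, however, the Protocol says so expressly; for an endoscopic lesion it does not. The end of AE follow-up at the last study visit applies to every participant and was not created by this rule.

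A reader might infer that the lesion goes unrecorded or that all safety follow-up stops. The right-hand column of the table shows otherwise. A reader might also infer that there is no early-termination visit, because the text of Section 5 describes none and Visit 5 is tied to Day 8 of Stage 2. That cannot be concluded: Section 5.0 refers to the Appendix I schedule and a procedures manual, neither of which is shown. Nor is the DAIDS manual that defines the expedited reporting level, so the exact events affected by closing the EAE period cannot be listed.

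Finally, sparing someone with visible pathology another 28 biopsies is a sound protective choice. It supports stopping gel and endoscopy, not ending observation.

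**Conclusion.** The point holds as an error of scope. Section 5.1.1 does not confine its withdrawal rule to findings before the first dose. Followed as written at Visit 3, it would take a dosed participant with a visible lesion out of scheduled visits, assured follow-up of non-serious AEs, and the active EAE reporting period.

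The size is small and uncertain. The Protocol gives no lesion rate, so the number of cases is unknown and may be zero. Each case would be one of 12 in its arm and would not be replaced, but with an unknown count that fraction measures no effect. The window is about 14 to 28 days per case, and no sample-size or detection figure changes. The conclusion assumes that site staff apply the sentence literally; staff who read it as a Visit 2 rule would avoid the problem. It is worth correcting because the correction is cheap and the participant concerned is one whose course matters for safety.

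**What to change.** In Section 5.1.1, limit withdrawal with re-screening to pathology found before the first dose of study gel. For pathology found after dosing, state that:

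- the finding is recorded and graded as an AE;
- gel is held at the investigator's discretion;
- the participant stays on study, off product if gel is held, with no further endoscopy or biopsy unless clinically safe;
- AE follow-up and EAE reporting continue until the AE resolves or stabilises, and at least to the nominal Week 6 time point.

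The cost is a few sentences of amendment and one or two extra safety contacts for any such participant. Those contacts need their own timing, because Visit 5 as written is anchored to Day 8 of Stage 2, which an off-product participant would not reach.
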